### Data Integrity

After data entry and validation, the data manager, principal investigator, project team, and statisticians will review the final database. This team will verify the database’s accuracy and integrity. Their review will result in the final definition of the analysis populations. The platform also includes features for follow-up reminders and oversight.

### Early Withdrawal

Participants may be withdrawn from the study for any of the following reasons: (1) incorrect enrollment of patients failing to meet inclusion or exclusion criteria, (2) nonadherence to required study procedures among eligible patients after enrollment, and (3) protocol deviations or incomplete data that compromise efficacy or safety assessments.

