### Randomization and Blinding

This is a single-blind trial in which patients and outcome assessors will be blinded to treatment allocation, while operating surgeons cannot be blinded because of the distinct intraoperative workflows associated with the navigation system and the freehand technique. Patients will remain blinded to their group assignment throughout the surgical procedure and the entire 12-month follow-up period, with the specific technique disclosed only after completion of all outcome assessments unless early unblinding is required for safety reasons. Radiographic assessors and functional outcome assessors will be blinded to group allocation, as all imaging studies and clinical assessments will be coded with unique participant identifiers and conducted without access to treatment assignment records. The primary statistical analyst will remain blinded until the final database is locked and all predefined analyses are completed, with group codes revealed only after the statistical analysis plan has been fully executed. Emergency unblinding may be performed by the principal investigator in the event of a serious adverse event for which knowledge of the intervention is essential for patient management, and any such event will be documented and reported.

Randomization will be performed by the coordinating center using a centralized computer-generated system with permuted blocks of 4 to ensure balanced allocation across treatment groups. Assignment details will be distributed to all participating sites via sequentially numbered, sealed opaque envelopes. All surgical procedures will be performed in accordance with the assigned randomization.

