### Statistical Plan

All statistical analyses will be performed using SPSS (version 26.0; IBM Corp), R (version 4.2.0; R Foundation for Statistical Computing), and Origin 2021 (version Origin 2021; OriginLab Corp), with a 2-sided significance level of *P*<.05. For the primary outcome (fluoroscopy frequency), group comparisons will be performed using a 1-sided *t* test or a Mann-Whitney *U* test, supplemented by a linear mixed-effects model with study site as a random effect to account for center-level clustering. Continuous secondary outcomes will be analyzed using similar linear mixed-effects models with baseline covariates, while categorical outcomes will be analyzed using generalized linear mixed-effects models with study site as a random intercept. For outcomes assessed repeatedly at 1, 3, 6, and 12 months, longitudinal mixed-effects models will include fixed effects for treatment group, time, and the group-by-time interaction, along with subject-specific random intercepts and slopes nested within site. Any baseline variable with a standardized difference >0.10 will be adjusted as a covariate. The center-by-treatment interaction will be formally tested; if significant (*P*<.10), exploratory subgroup analyses stratified by site will be conducted. Predefined subgroup analyses include age, gender, Garden classification, and fracture side. Sensitivity analyses will include per-protocol and as-treated analyses.

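### The withdrawal grounds and a population decision taken from the completed database leave room to remove randomized patients before the primary comparison is formed

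*Protocol article*

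**What the plan says.** The Early Withdrawal section of the protocol article gives three grounds on which an enrolled participant may be withdrawn: "incorrect enrollment of patients failing to meet inclusion or exclusion criteria", "nonadherence to required study procedures among eligible patients after enrollment", and "protocol deviations or incomplete data that compromise efficacy or safety assessments". It does not say whether data already recorded for a withdrawn participant are still analyzed.

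The Data Integrity section states that, once the data have been entered and checked, "the data manager, principal investigator, project team, and statisticians will review the final database". It adds: "Their review will result in the final definition of the analysis populations".

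On blinding, the Randomization and Blinding section says "operating surgeons cannot be blinded because of the distinct intraoperative workflows". It also says "The primary statistical analyst will remain blinded until the final database is locked and all predefined analyses are completed". It gives no blinding rule for the team that settles the populations.

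On analysis sets, the Statistical Plan says only "Sensitivity analyses will include per-protocol and as-treated analyses". It does not name the set for the main analysis. The Results section lists technical failures and device deficiencies among the feasibility metrics and gives no rule for how such cases enter the primary comparison.

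**The concern.** The primary outcome is the number of fluoroscopic images during surgery, so it is complete when the operation ends. A withdrawal decided after that cannot be needed because the outcome is missing. The third ground is a judgment on whether a patient can be evaluated, and it can be made by people who know the arm and the count.

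The population decision comes at the end, with every primary outcome on file. The protocol blinds the analyst, but the principal investigator and project team also sit in the review. Image counts are to be split by surgical phase, and the navigational positioning phase exists only in the navigated arm. Anyone who sees phase-level counts can therefore tell the arm.

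The exposure is uneven between arms. A navigated operation that is finished freehand can arise in one arm only and would probably carry a high image count. The protocol requires operations to follow the allocation, so such a case could be treated as a deviation, although the document does not say so. If cases of this kind were withdrawn or left out of the populations, the estimate would shift toward navigation.

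**Working it through.** **Inputs (protocol article, Sample Size).** Control mean 32.2 (SD 5.2); navigated mean 15.2 (SD 3.7); superiority margin 15.4; one-sided α 0.025; power 0.80; 126 per group, raised to 150 for 15% dropout.

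**The plan's own figure.** Planned difference: 32.2 − 15.2 = 17.0. Excess over the margin: 17.0 − 15.4 = 1.6. Pooled SD: √[(5.2² + 3.7²)/2] = √[(27.04 + 13.69)/2] = 4.513. The normal approximation gives n = (27.04 + 13.69) × (1.960 + 0.842)² / 1.6², about 124.9, so 125 per group. The noncentral t version gives 126, as stated. Dropout: 126/0.85 = 148.2, so 149, set at 150. The stated size reproduces with a test against 15.4.

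**Illustration.** The document gives no conversion rate, so a fraction f of the navigated arm is assumed to be finished freehand, with the freehand mean and SD.

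- Navigated mean, all kept: 15.2 + 17f. Difference as randomized: 17.0 − 17f.
- Navigated variance, all kept: (1 − f)·3.7² + f·5.2² + f(1 − f)·17².
- Power, all kept: Φ[(17.0 − 17f − 15.4)/SE − 1.96], with SE² = 27.04/150 + variance/150.
- Power, converted cases removed from the navigated arm only: Φ[1.6/SE − 1.96], with SE² = 27.04/150 + 13.69/[150(1 − f)].

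Worked at f = 5%:

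- Kept: variance = 13.01 + 1.35 + 13.73 = 28.09; SE = √[(27.04 + 28.09)/150] = 0.606; Φ(0.75/0.606 − 1.96) = Φ(−0.72), about 24%.
- Removed: SE = √(27.04/150 + 13.69/142.5) = 0.526; Φ(1.6/0.526 − 1.96) = Φ(1.08), about 86%.

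| Assumed conversion | Navigated patients (of 150) | Difference as randomized | Power, kept | Power, removed |
|---|---|---|---|---|
| 0% | 0 | 17.00 | 87% | 87% |
| 2% | 3 | 16.66 | 62% | 86% |
| 5% | 7–8 | 16.15 | 24% | 86% |
| 10% | 15 | 15.30 | 2% | 85% |

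Each 1% of conversion lowers the as-randomized difference by 0.17 images. It reaches the margin at f = 1.6/17 = 9.4%. At and beyond that point a claim of superiority over 15.4 would be false for the as-randomized difference, yet removal would still produce it about 85% of the time.

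**Dependence on the margin.** Against a zero difference at 10% conversion, the as-randomized difference of 15.3 is about 15.3/0.674 = 22.7 standard errors. Power is then essentially 100% whether the cases are kept or removed.

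**The case against.** Several points on the other side are sound.

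- Withdrawal from a study is not the same as removal from its analysis, and the Early Withdrawal section speaks only of the former. This stands as a reading. The document does not state it, and its third ground is worded in terms of efficacy assessment.
- Calling per-protocol and as-treated sensitivity analyses makes sense only if the main analysis is neither. This stands as an implication. A reader might infer that the main set is really a per-protocol set, and the text does not support that. It leaves open who has been removed before the main set is formed.
- A reader might infer that navigation failures count as deviations and will be excluded. No section says so. The Safety Events section covers malfunction and performance failure under device deficiency, and the Results section lists technical failures as a performance metric and handles deviations separately.
- A statistical analysis plan may define the sets, and a review before database lock that assigns patients to predefined sets is normal practice. The missing name of a set is therefore not the point. The point is that the protocol states a withdrawal rule based on evaluability and a population decision made from the final database, without arm-blinding for those who decide.
- The analyst's blinding helps, but it does not cover the principal investigator or the project team.

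**Conclusion.** The concern holds as a matter of what the stated rules permit, not of what the team intends. Taken together, the Early Withdrawal and Data Integrity sections allow randomized patients to be removed after their primary outcome is known, by people not stated to be blinded, before the implied as-randomized set is formed.

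The possible size is large but conditional. It rests on an assumed conversion rate, on freehand-level counts in converted cases, on removal from the navigated arm only, and on a test against 15.4. The sample size is built on that margin, but the Statistical Plan does not repeat it for the test. Under these assumptions, power with converted cases kept falls from 62% at 2% conversion to 2% at 10%, while removing them holds it at 85% to 86%. A reader might take this as a forecast for the trial or as a loss of power under any test. It is neither: the document gives no conversion rate, and against zero the conclusion would hardly change.

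**What to change.** - In Early Withdrawal, state that withdrawal on these grounds ends follow-up only and does not remove the patient from the primary analysis. The grounds themselves need not be deleted; the analysis problem does not require a new rule for when participation ends.
- In the Statistical Plan, define the primary set now: all randomized patients who start surgery, analyzed in the allocated arm, with every recorded image counted, including those after a technical failure or conversion.
- In Data Integrity, limit the review before database lock to assigning patients to the per-protocol and as-treated sensitivity sets by prespecified criteria, blinded to arm and to fluoroscopy counts. Phase-level counts should be withheld from that review because they reveal the arm.

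The cost is an amendment to wording in the protocol and the analysis plan. The article reports that recruitment is ongoing and that no analysis has been done, so the change can still be made before the data are reviewed. No change in sample size follows from it. The estimated benefit may turn out slightly less favorable to navigation.

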### Statistical Plan

All statistical analyses will be performed using SPSS (version 26.0; IBM Corp), R (version 4.2.0; R Foundation for Statistical Computing), and Origin 2021 (version Origin 2021; OriginLab Corp), with a 2-sided significance level of *P*<.05. For the primary outcome (fluoroscopy frequency), group comparisons will be performed using a 1-sided *t* test or a Mann-Whitney *U* test, supplemented by a linear mixed-effects model with study site as a random effect to account for center-level clustering. Continuous secondary outcomes will be analyzed using similar linear mixed-effects models with baseline covariates, while categorical outcomes will be analyzed using generalized linear mixed-effects models with study site as a random intercept. For outcomes assessed repeatedly at 1, 3, 6, and 12 months, longitudinal mixed-effects models will include fixed effects for treatment group, time, and the group-by-time interaction, along with subject-specific random intercepts and slopes nested within site. Any baseline variable with a standardized difference >0.10 will be adjusted as a covariate. The center-by-treatment interaction will be formally tested; if significant (*P*<.10), exploratory subgroup analyses stratified by site will be conducted. Predefined subgroup analyses include age, gender, Garden classification, and fracture side. Sensitivity analyses will include per-protocol and as-treated analyses.

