**Methods:**

This multicenter, prospective, randomized controlled superiority trial will compare navigation system–assisted TCS fixation with conventional freehand TCS fixation in patients with FNF from June 2024 to October 2026. Eligible participants are adults aged ≥18 years diagnosed with FNF who are indicated for internal fixation. The primary outcome is the frequency of intraoperative fluoroscopy. Secondary outcomes include the neck-shaft angle, guide wire placement quality, operative time, intraoperative blood loss, fracture healing status, the Harris Hip Score, the 36-Item Short Form Health Survey, and the Zarit Caregiver Burden Score. The sample size calculation indicated that 150 (50%) participants per group (N=300) would be needed to detect a superiority margin of 15.4 fluoroscopy images with 80% power and a 1-sided α of .025, accounting for a 15% dropout rate. All patients will undergo 12 months of follow-up. Data analysis will compare groups using 1-sided *t* tests and Mann-Whitney *U* tests, supplemented by linear mixed-effects models with study site as a random effect.

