**(2)**

In these equations, 1–α denotes the significance level, *1–β* represents the statistical power, *Z_1−α_* and *Z_1−β_* are critical values derived from the Z-table, *σ* refers to the SD of the 2 groups, *δ* indicates the mean difference between groups, and *Δ* stands for the superiority margin.

According to published literature, the mean number of intraoperative fluoroscopies in screw fixation for FNFs is approximately 32.2 times [26], while the use of a navigation system is expected to significantly reduce fluoroscopy frequency. On the basis of preliminary pilot data and the experience with navigated procedures at our institution, the mean (SD) number of fluoroscopy images for the control group (nonnavigated) is 32.2 (SD 5.2), and that for the experimental group (navigated) is 15.2 (SD 3.7). The superiority margin was set at 15.4, with a 1-sided significance level of .025 and a statistical power of 0.8.

With a 1:1 allocation ratio between the 2 groups, the sample size calculation was performed using the aforementioned formula and PASS (version 15.0; NCSS LLC) software. Considering patient recruitment feasibility, each group required 126 participants, yielding a total of 252 subjects. After accounting for a 15% dropout rate and distribution across multiple centers, the final sample size was set at 150 (50%) per group, resulting in a total of 300 participants.

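### The Statistical Plan does not secure the 1-sided 2.5% error rate behind the sample size: its only threshold is a 2-sided .05, set beside a 1-sided primary test that may be either of two tests

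*Protocol article*

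**What the plan says.** **Level used for design.** The Sample Size section plans the primary outcome "with a 1-sided significance level of .025 and a statistical power of 0.8". The abstract agrees: "with 80% power and a 1-sided α of .025, accounting for a 15% dropout rate".

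**Level given for analysis.** The Statistical Plan opens with a single level for all analyses, "with a 2-sided significance level of *P*<.05". The .025 does not reappear in that section.

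**Primary test.** The next sentence of the Statistical Plan says that "group comparisons will be performed using a 1-sided *t* test or a Mann-Whitney *U* test". It gives no rule for choosing between them and no sidedness for the Mann-Whitney test. The abstract words this differently: "Data analysis will compare groups using 1-sided *t* tests and Mann-Whitney *U* tests".

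**Role of site.** The primary comparison is "supplemented by a linear mixed-effects model with study site as a random effect to account for center-level clustering". Neither of the two tests named first contains site.

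**The concern.** The section that governs the analysis contains one threshold, .05, and places it next to a 1-sided primary test. An analyst who follows that section literally would compare a 1-sided P value with .05 and run the trial at twice its design error rate.

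Three analyses are also named for one outcome, and the document does not say which of them decides the trial. If the choice is made after the P values are known, the error rate rises further. What is at stake is whether a positive result can be reported as significant at the 2.5% level for which the trial was sized.

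**Working it through.** **Inputs (Sample Size section).** Control mean 32.2, SD 5.2; navigated mean 15.2, SD 3.7; margin 15.4; 1-sided .025; power 0.8; 1:1 allocation; 126 per arm before dropout and 150 after.

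**1. Reproduce the stated sample size.** The effective difference is (32.2 − 15.2) − 15.4 = 1.6. The sum of the variances is 5.2² + 3.7² = 27.04 + 13.69 = 40.73.

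n per arm = 40.73 × (1.960 + 0.842)² / 1.6² = 124.9, so 125. The noncentral t version gives 126 (power 0.8005), as stated. Dropout: 126 / 0.85 = 148.2, so 149, which the plan rounds to 150.

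**2. Compare the two levels.**

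| Rule applied to the primary test | Critical value | n per arm (normal approximation) | Power at 126 | Error rate |
|---|---|---|---|---|
| 1-sided P < .025 | 1.960 | 125 | 0.80 | 2.5% |
| 2-sided P < .05 | 1.960 | 125 | 0.80 | 2.5% in the favourable direction |
| 1-sided P < .05 | 1.645 | 99 | 0.88 | 5% |

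The last n is 40.73 × (1.645 + 0.842)² / 2.56 = 98.4, so 99. The first two rows are the same test for a directional conclusion. Only the third, which the Statistical Plan permits but does not state, doubles the error. The stated 126 confirms that the design used the 1.960 rule.

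**3. Open choice of test.** Trials were simulated with 150 per arm, zero true difference, and 20,000 runs per scenario. The smaller of the 1-sided t and Mann-Whitney P values was taken each time.

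| Data (no site effect) | Better of two at .025 | Better of two at .05 |
|---|---|---|
| Normal | 2.9–3.0% | 5.8–6.0% |
| Skewed (gamma, shape 2) | 3.5% | 6.7% |

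Each test alone kept close to its nominal level. The choice of test therefore adds roughly half to one percentage point at .025. The figure near 6% needs both the .05 threshold and the better-of-two choice. The sample size, by contrast, comes from the margin hypothesis. Data shifted to a true difference equal to the margin, with the plan's unequal SDs, again gave about 3% and 6%.

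**4. Leaving site out.** The document gives neither the number of sites nor the between-site share of variance. With 10 equal sites assumed, the t test at 1-sided .025 had these error rates:

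| Between-site share of variance | Allocation blocked by site | Blocks not tied to site |
|---|---|---|
| 0 | 2.4% | 2.6% |
| 0.05 | 2.2% | 2.6% |
| 0.20 | 1.5% | 2.5% |

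Individual randomization protects the error rate in both columns. Blocking by site makes the unadjusted test conservative, because between-site variation stays in its error term although the arms are balanced on it.

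**The case against.** The strongest reply is that there is no conflict. The level for the primary outcome is fixed twice, in the abstract and in the Sample Size section, and a 2-sided .05 is the same criterion for a directional claim. The general sentence in the Statistical Plan can be read as that equivalent, and nothing says that a 1-sided P value will be judged at .05. This stands to the extent that a reader who infers that the error rate **is** something other than 2.5% goes too far. The document leaves 2.5% unsecured; it does not show it to be false.

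A t test or Mann-Whitney is also common shorthand for a choice by distribution, with the rule left to the analysis plan. The Randomization and Blinding section keeps the primary analyst blinded until the predefined analyses are done. Both points weaken the assumption that the more favourable result would be picked. They do not settle which analysis decides the trial, and the or in the Statistical Plan still differs from the and in the abstract. The abstract sentence may, however, be summarising all outcomes at once.

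A reader might also infer that ignoring site inflates false positives or costs the trial its power. The first is wrong in direction, as shown above. The second needs two things that the document does not give. One is allocation blocked within site, which the recruitment section suggests by mentioning a site scheme but which Randomization and Blinding does not state. The other is planning SDs that are purely within-site. Under those assumptions, with 10–30% of variance between sites, unadjusted power at 150 per arm would be 84–77%, against 87% with site in the model. If the SDs are total SDs, unadjusted power would be 88–91%. No power loss is claimed here.

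**Conclusion.** The concern holds as an unsecured decision rule. The sample size uses a 1-sided .025, while the analysis section offers only .05 beside a 1-sided test, two interchangeable tests and a supplementary model.

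- **Threshold:** 2.5% if the two levels are read as equivalent, and 5% if the 1-sided P value is judged at .05. This follows from the levels themselves and needs no further assumption.
- **Choice of test:** about 3% at .025, or about 6% at .05, if the better of the two results is taken. This rests on simulation at a zero-difference null with normal outcomes, and is slightly higher with skewed ones.
- **Site:** no inflation. The unadjusted test is conservative if allocation is blocked by site, by an amount that depends on an unknown between-site variance.

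The sample size is sound for the 1-sided .025 that it states. The matter should be settled now: recruitment is ongoing and no analysis has been done, so a choice made today cannot be driven by results.

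**What to change.** In the Statistical Plan, state that the primary outcome is tested once, at 1-sided P<.025, or equivalently by the matching limit of a 2-sided 95% confidence interval for the difference. Name one primary analysis before data are seen. The linear mixed model with treatment and site is the natural choice, because it is already planned and accounts for site. Label the t test and the Mann-Whitney test as sensitivity analyses, and give the sidedness of each. Restrict the 2-sided .05 to secondary outcomes. Bring the abstract into line.

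The cost is about one paragraph of protocol wording, with the same text in the analysis plan. Sample size, allocation and data collection do not change.

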### Outcomes and Measures

#### Primary Outcome

The total number of intraoperative fluoroscopic images will be recorded for both groups. This includes each anteroposterior and lateral view obtained, starting from fracture reduction. To minimize observer bias, fluoroscopic counts will be categorized and analyzed separately for fracture reduction, navigational positioning, and implant placement.

Fluoroscopy frequency was selected as the primary outcome for this superiority trial for the following reasons. First, the number of intraoperative fluoroscopic images is an objective, quantifiable, and operator-independent measure that directly reflects the efficiency and precision of guide wire and screw placement. Second, reducing radiation exposure is a major clinical advantage of navigation-assisted surgery, as it lowers occupational radiation risk for surgical staff and potential patient harm. Finally, fluoroscopy frequency is significantly correlated with operative time, surgical accuracy, and the learning curve, making it a valid surrogate end point for overall surgical quality. Therefore, a reduction in fluoroscopy frequency with the navigation system, compared with the freehand technique, would support the superiority of the navigation system in terms of surgical efficiency and safety.

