## Discussion

### Principal Findings

This multicenter, prospective, randomized controlled trial is designed to determine whether the StarNav-1 intelligent navigation system is superior to the conventional freehand technique for TCS fixation of FNF. Upon completion, we anticipate that the primary outcome will be significantly lower in the navigation-assisted group than in the freehand group. This hypothesis is informed by prior studies that have reported reductions in radiation exposure with navigation-assisted techniques [15,21,27,28]. On the basis of the existing literature, we also anticipate that secondary outcomes, including guide wire placement quality, neck-shaft angle restoration, operative time, and intraoperative blood loss, will favor the navigation group [16-18]. However, as this is a protocol for an ongoing trial, all findings remain to be empirically tested.

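### The 15.4-image superiority margin that sizes the trial is not carried into the stated primary analysis or the success wording

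*Protocol article*

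**What the plan says.** The Sample Size section treats the expected difference and the margin as two separate quantities: δ "indicates the mean difference between groups, and *Δ* stands for the superiority margin". It then fixes the design: "The superiority margin was set at 15.4, with a 1-sided significance level of .025 and a statistical power of 0.8". The planning values are 32.2 images (SD 5.2) for control and 15.2 (SD 3.7) for navigation. The result is that "each group required 126 participants, yielding a total of 252 subjects", raised to 150 per group for 15% dropout and spread over centers. The Abstract repeats the margin, and Strengths and Limitations cites it as prespecified and as a basis for power.

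Three later places bear on how the result will be judged:

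- Statistical Plan: "group comparisons will be performed using a 1-sided *t* test or a Mann-Whitney *U* test", supplemented by a mixed model with site as a random effect. The section sets a general 2-sided .05 level and mentions neither a margin nor a confidence-limit criterion.
- Primary Outcome: "Therefore, a reduction in fluoroscopy frequency with the navigation system, compared with the freehand technique, would support the superiority of the navigation system".
- Principal Findings: "we anticipate that the primary outcome will be significantly lower in the navigation-assisted group than in the freehand group".

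Nowhere does the article say that superiority requires a reduction of more than 15.4 images.

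**The concern.** A trial sized for superiority by a margin tests a different hypothesis from one that asks whether there is any difference. The first must rule out reductions up to 15.4 images; the second need only rule out zero. If the analysis is run in the form that software gives by default, the trial could claim superiority on a hypothesis for which it was not sized. The 300-patient rationale, the 80% power and the claim would then not belong together.

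Naming the Mann-Whitney test as an alternative adds to the problem. In its usual form it has no 15.4-image null, and with SDs assumed unequal (5.2 and 3.7) it is not a test of the difference in means, which is the quantity that the margin is defined on.

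**Working it through.** **Inputs** (Sample Size section): means 32.2 and 15.2, so δ = 17.0; SDs 5.2 and 3.7; margin Δ = 15.4; 1-sided α = .025; power 0.80; 126 evaluable and 150 enrolled per arm.

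**1. Reproduce the stated sample size.**
- Sum of variances: 5.2² + 3.7² = 27.04 + 13.69 = 40.73. The root-mean-square SD is √(40.73/2) = 4.513.
- Powered distance: 17.0 − 15.4 = 1.6.
- Normal approximation: n = 40.73 × (1.960 + 0.842)² / 1.6² = 40.73 × 7.849 / 2.56 = 124.9, so 125 per arm.
- Noncentral t: power is 0.7973 at 125 and 0.8005 at 126, so 126 per arm, as stated.
- Dropout: 126 / 0.85 = 148.2, so 149, rounded to 150.

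The sample size is right for H0: control − navigated ≤ 15.4. Without subtracting the margin, the same inputs need about 3 per arm (92% power by t). The stated 126 is therefore explained by the margin hypothesis and not by a zero null.

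**2. Smallest observed reduction that gives significance at 1-sided .025.** Threshold = null value + t(0.975, 2n − 2) × √(40.73/n).

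| n per arm | SE | Null = 0 | Null = 15.4 |
|---|---|---|---|
| 126 | 0.569 | 1.12 | 16.52 |
| 150 | 0.521 | 1.03 | 16.43 |

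If the 2-sided .05 level were misread as 1-sided .05, the thresholds would be 0.94 and 16.34 (126 per arm) or 0.86 and 16.26 (150 per arm). The gap between the columns stays at 15.4.

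**3. Power under each reading.**
- Margin null, true reduction 17.0: 80.0% at 126 per arm (t) and 86.7% at 150 (normal approximation).
- Zero null, true reduction 1.5: 75% at 126 and 82% at 150.

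**4. Sensitivity to the SD (assumed values).** With a common SD of 8 to 12 images, the zero-null threshold at 126 to 150 per arm lies between about 1.8 and 3.0 images, still far below 15.4.

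**5. Where the readings part.** Any observed reduction from about 1 to about 16.4 images is a success under a zero null and a failure under the design hypothesis. The Introduction reports a pilot reduction of about 15.2 images, whereas the Sample Size section gives 15.2 as the navigated mean. If the true reduction were 15.2, power against the margin would be about 1% at 126 per arm, while a zero-null test would be almost certain to succeed.

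**The case against.** The strongest reply is that the Statistical Plan states no null value. A 1-sided t test can be run against a shift of 15.4, and the margin is given in the Abstract, in Sample Size and in Strengths and Limitations. Read together, those sections are compatible with a margin test. This stands: a reader might infer that the protocol specifies a test against zero and will declare superiority on about 1 image, but the text does not say so. The displayed equations are also not available here, so the margin null is inferred from the definitions and from the arithmetic that returns 126.

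It is also fair that the Primary Outcome sentence closes a rationale for choosing the endpoint and that the Principal Findings sentence is a forecast. Neither is a formal decision rule, and it would be too strong to say that the article makes any significant reduction its success criterion. The Introduction points the other way, since it asks for a reduction that matters clinically as well as statistically.

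A third reply is that an analysis plan, not shown, may supply the null value. That would settle how the test is run. It would not align the published sections: the one that sizes the trial uses a margin, while those that name the tests and describe what would support superiority do not. The Mann-Whitney test can address a margin if the data are shifted, but the article does not mention shifting.

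**Conclusion.** The concern holds as a gap between the design hypothesis and the stated analysis. The sample size is correct for a margin of 15.4 images, but nothing in the Statistical Plan or the success wording uses that margin. The decision threshold is thus undetermined between about 1.0 to 1.1 images (zero null) and 16.4 to 16.5 images (design hypothesis). These figures assume the article's SDs, normal-theory tests at 1-sided .025, and 126 to 150 analyzed patients per arm.

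Two stronger inferences are not supported: that a zero null has been specified, and that the sample size is wrong. The point still needs to be settled before any analysis, because it concerns the primary hypothesis and the two readings disagree over almost all reductions below the planned 17.0.

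**What to change.** - In the Statistical Plan, state H0: mean(control) − mean(navigated) ≤ 15.4, tested at 1-sided .025, and confine the 2-sided .05 level to the other analyses.
- Declare superiority only if the lower limit of the 2-sided 95% CI for the mean difference exceeds 15.4.
- Make the unequal-variance t comparison primary. Keep Mann-Whitney only as a sensitivity analysis on data shifted by 15.4.
- Align the wording in Primary Outcome and Principal Findings with this rule.
- If a zero-null result is also reported, label it as not the hypothesis for which the trial was sized.

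Dropping the margin is not an equivalent repair. The article calls it prespecified and recruitment is under way, so removing it would lower the bar mid-trial.

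The cost is a wording change to the protocol and analysis plan, documented and disclosed as the Results section promises for significant amendments. No extra patients are needed. The downside is that success is harder than under a zero-null test. The article reports that no data analysis had been performed at submission, so the change can still be made before results are known.
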